#### **iv. Regimen monitoring and measurements by the un-blinded investigator**

- a. At t= 5, 6, 10, 15, 20, 25, 26, 30, 35 record the time and SpO2.
- b. Monitor the SpO2 and if the nasal cannulae oxygen flow is changed, document the time and new oxygen flow (air driven regimen only).
- c. Document the time the nebulised medication canister becomes empty.
- d. As close as possible prior to the completion of the second nebuliser at t=35 minutes, a CBG measurement will be taken, as per the SOP. On visualisation of blood entering the capillary tube un-blinded investigator ask blinded investigator to record the time and PtCO2. The CBG will be taken whilst the air/oxygen-driven nebuliser is still in place: if the investigator runs into technical difficulties (for example, slow blood flow when collecting CBG sample), then the nebuliser shall be removed at no later than t=37 minutes.

NOTE: The t=20 measure is to occur immediately prior to initiation of the 2nd nebuliser and the t= 15 and t=35 measures are to occur immediately prior to cessation of nebuliser delivery. In the event of a PtCO2 rise of ≥10mmHg

from baseline whereby a nebuliser has to be terminated early, the CBG measurement will be taken at this time-point. The top priority if this occurs is removal of oxygen and clinical assessment of the patient. CBG MUST OCCUR AFTER THIS.

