## **iv. Roles of the un-blinded investigator**

- a. Recording medical history, demographics and obtaining written informed consent (either investigator can do this prior to blinding).
- b. CBG sampling
- c. Randomisation
- d. Administration of the randomised intervention
- e. Recording and monitoring of finger probe SpO2
- f. Increase oxygen therapy if SpO2 <85%.

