### Oxygen driven nebuliser regimen

- a. t=0-15 min: 2.5 mg salbutamol by nebulisation, delivered by oxygen at a flow rate of 8L/min
- b. t=15-20 min: Removal of nebuliser mask

- c. t=20-35 min: 2.5 mg salbutamol by nebulisation, delivered by oxygen at a flow rate of 8L/min.

The nebuliser is to continue running for the entire 15 minutes at t=0-15 min and t=20-35 min, even if the bronchodilator medication has dissipated.

Any nasal cannulae oxygen therapy is to be discontinued and nasal prongs removed, during t=0-15 min and t=20-35 min. Oxygen must be restarted at the same flow given prior to nebuliser delivery (i.e. at t=15 the oxygen must be started at the flow delivered at t=0, and at t=35 it must be started again at the flow delivered at t=20 minutes). Note that if the patient was not receiving oxygen before the intervention (was breathing room air) this will continue unless the oxygen saturations drop to <85%. If this occurs the nebuliser mask will be removed, nasal prongs attached and oxygen given. If this does happen it will be recorded in the case report form.

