### D. SECONDARY OUTCOME VARIABLES

- i.  $P_{\text{capCO}_2}$  at completion of the second nebulisation (immediately prior to  $t=35\text{min}$ ), adjusted for baseline  $P_{\text{capCO}_2}$ .
- ii. pH at completion of the second nebulisation (immediately prior to  $t=35\text{min}$ ), adjusted for baseline.
- iii.  $P_t\text{CO}_2$  at six minutes after the initiation of the first and second nebulisers ( $t=6\text{min}$  and  $t=26\text{min}$ )
- iv.  $P_t\text{CO}_2$ ,  $\text{SpO}_2$  and heart rate at 5 minute intervals from  $t=0$  to  $t=80\text{min}$

- v. Greatest PtCO2 change from baseline at any of the recorded time points between t=0 and t=35 minutes when the nebuliser is in place.
- vi. Proportion of participants with  $\geq 4$ mmHg (physiologically significant) and  $\geq 8$ mmHg (clinically significant) increase in PcapCO2 or PtCO2 from baseline
- vii. Number of intervention terminations due to a rise in PtCO2  $\geq 10$ mmHg
- viii. The proportion of patients with a reduction in pH of  $\geq 0.06$  from baseline
- ix. Proportion of patients who required initiation of an increase in the flow of oxygen therapy during the regimen and observation periods.

NOTE: PtCO2 measurements recorded and analysed will be the actual (raw) data from the Transcutaneous Monitoring System, but adjustments for 'drift' will also be reported upon.

---

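### During the regimen, nasal oxygen flow changes are logged in the air arm only, although secondary outcome ix compares flow increases over that period between arms

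*Protocol*

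**What the plan says.** - **Flow log during the regimen.** Section 6.E.iv, item b, covers t=0-35. When nasal flow is changed, the un-blinded investigator is to "document the time and new oxygen flow (air driven regimen only"). The matching instructions for the wash-in (6.D.iii, item b) and for the post-regimen period (6.F.ii, item b) name no arm.
- **Oxygen-arm nasal flow.** Section 6.E.iii removes nasal oxygen during both nebulisations and restores it in between, with a reference flow for each restart (the second being the t=20 flow): "at t=15 the oxygen must be started at the flow delivered at t=0, and at t=35 it must be started again at the flow delivered".
- **Rescue.** Section 4.B.iv, item f, gives the un-blinded investigator the role "Increase oxygen therapy if" SpO2 is below 85%, with no limit by arm or period.
- **Case report form entry in the oxygen arm.** The rescue text in 6.E.iii begins "Note that if the patient was not receiving oxygen before the intervention (was breathing room air) this will continue unless the oxygen saturations drop to" below 85%, and ends "If this does happen it will be recorded in the case report form". The air-arm text has a parallel entry.
- **Outcome.** Section 7.D, item ix: "Proportion of patients who required initiation of an increase in the flow of oxygen therapy during the regimen and observation periods". Section 7.A says that outcomes are compared between the two regimens.

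**The concern.** Outcome ix is a between-arm comparison, so an increase in flow must have the same chance of being recorded in each arm. For the regimen period the protocol gives the air arm a timed log and excludes the oxygen arm from it. The exclusion makes sense while oxygen-arm prongs are off (t=0-15 and t=20-35), but not at t=15-20, when nasal oxygen is running again after 15 minutes of oxygen-driven nebulisation.

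The protocol itself allows for a change of flow in those five minutes. It uses the t=0 flow for the restart at t=15 and the t=20 flow for the restart at t=35, a distinction that matters only if the two can differ. The person recording knows the allocation, which makes identical recording rules more important.

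At stake is an under-count of outcome ix in one arm, created by the recording rule. A fall in SpO2 that was corrected before the t=20 reading could also leave a t=20 value with no note that flow had been raised.

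**Working it through.** The protocol gives no figure on this point to reproduce. The check sets the recording rules side by side for each situation in which nasal flow could be raised.

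| Situation | Required record | Time of change required? |
|---|---|---|
| Air arm, any change, t=0-35 | Log entry with new flow (6.E.iv, b) | Yes |
| Oxygen arm, on room air, rescued below 85% | Case report form entry (6.E.iii) | Not stated |
| Oxygen arm, on nasal oxygen, raised at t=15-20 and still raised at t=20, second nebuliser completed | None direct; inferred if the flow documented at the end of the second nebuliser (6.F.i) exceeds the t=0 flow (6.E.i) | No |
| Oxygen arm, on nasal oxygen, raised and back to the t=0 flow before t=20 | None | No |
| Oxygen arm, on nasal oxygen, raised, regimen stopped before the second nebuliser ends | Possibly none: the 6.F.i entry is tied to the end of that nebuliser | No |
| Either arm, change after the regimen | Log entry with new flow (6.F.ii, b) | Yes |

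The inference in the third row works because 6.F.i defines the oxygen-arm flow after the second nebuliser as the t=20 flow. A lasting raise therefore appears as a difference between two recorded values. The protocol does not say that outcome ix is derived in this way.

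The fifth row arises because sections 6.E.iv and 6.E.v end the intervention early if PtCO2 rises by 10 mmHg or more. Under hypothesis i (section 2.C) this would be expected more often in the oxygen arm.

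**Scale.** Ninety patients at 1:1 give 90 / 2 = 45 per arm. One missed participant lowers the oxygen-arm proportion by 1 / 45 = 2.2 percentage points.

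The protocol gives neither the true proportion needing an increase (p) nor the share of oxygen-arm participants with an increase who leave no trace (m). If p is the same in both arms, the false difference is p × m and the number missed is 45 × p × m. With assumed values only:

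- p = 10%, m = 10%: 0.10 × 0.10 = 1.0 point; 45 × 0.01 = 0.45 participants.
- p = 20%, m = 25%: 0.20 × 0.25 = 5.0 points; 45 × 0.05 = 2.25 participants.
- p = 30%, m = 50%: 0.30 × 0.50 = 15 points; 45 × 0.15 = 6.75 participants.

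These values show how the error scales and are not estimates. Only participants whose sole increase fell in the fourth or fifth row count towards m, if the inference in the third row is actually made.

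**The case against.** The strongest reply is that little is truly lost. Room-air rescues are entered in the case report form in both arms. A raise that persists to t=20 can be recovered from two required flows, and outcome ix needs a yes or no, not a time. The oxygen-arm text provides for no titration at t=15-20, so a raise fully reversed within five minutes is not a planned step. Nasal oxygen is off for 30 of the 35 minutes in that arm, which probably explains the restriction. All of this stands and makes the gap narrow. It does not close it: the recovery is indirect and not prescribed, and it fails for a reversed raise and possibly after early termination.

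A reader might also infer more than the protocol supports:

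- **That rescue oxygen in the oxygen arm goes unrecorded altogether.** The room-air entry and the inferable lasting raise contradict this.
- **That desaturation is monitored or recorded less in the oxygen arm.** Section 4.B.iv, item e, assigns SpO2 monitoring without limit by arm, and 6.E.iv, item a, sets the same reading times for both arms, including t=15 and t=20. At most, a dip corrected between those readings is missed.
- **That the test of rebound hypoxaemia (hypothesis v) is compromised.** Section 8.A places that assessment in the observation period, where flow changes are logged in both arms.

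**Conclusion.** The point holds as a narrow recording bias in one secondary outcome. The regimen-period flow log excludes the oxygen arm, yet outcome ix counts regimen-period increases in both arms. The participants exposed are those in the oxygen arm already on nasal oxygen whose flow is raised at t=15-20. Any loss lowers the oxygen-arm count only.

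The number of missed events cannot be estimated: the protocol gives neither the proportion on nasal oxygen at t=0 nor a rate of flow increases. Counting every raise in the window as lost would be wrong, because a raise kept to t=20 can be inferred when the second nebuliser is completed. The primary outcome, PtCO2 at t=35, does not depend on these records, and the planned rebound assessment at t=35-80 is unaffected.

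A separate limit on outcome ix remains even with equal recording. Air-arm flow is titrated throughout the regimen, while oxygen-arm flow is restarted at a fixed value, so increases are more likely to arise in the air arm by design.

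**What to change.** Delete the four-word restriction to the air arm from section 6.E.iv, item b, so that the time and new value of any nasal flow change are logged identically in both arms from t=0 to t=35. Add two case report form entries for the oxygen arm: nasal flow after the t=15 restart and nasal flow at t=20. The second also documents directly the value on which the t=35 restart depends ("at t=35 it must be started again at the flow delivered at t=20 minutes") and remains available if the second nebulisation is stopped early. Sections 4.B.iv, 6.E.iii, 6.E.iv, 6.F.i and 7.D should then be read together so that the recording rules match outcome ix.

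The cost is a short deletion and two fields, completed by an investigator who is already recording SpO2 at those times. Only data recording changes; no rule for giving oxygen is altered. The change needs to be made before the visits concerned, because the time of an unlogged change cannot be recovered afterwards.

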**v. Regimen monitoring and measurements by the blinded investigator**

- a. At t= 5, 6, 10, 15, 20, 25, 26, 30, 35 record the time, PtCO2 and heart rate.
- b. Continuously monitor PtCO2, and should it increase by  $\geq 10$ mmHg from baseline measure (t=0), indicate this to the un-blinded investigator so they can terminate the regimen intervention.
- c. Record the time and PtCO2 during arterialised earlobe blood gas sampling, as prompted by the un-blinded investigator.

NOTE: The t=20 measure is to occur immediately prior to initiation of the 2nd nebuliser and the t= 15 and t=35 measures are to occur immediately prior to cessation of nebuliser delivery

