### B. OUTCOME MEASUREMENTS

Capillary blood gas samples (CBG) will measure  $p\text{CO}_2$  ( $P_{\text{capCO}_2}$ ) and pH. The samples will be collected in capillary tubes and analysed at the Wellington Regional Hospital or Hutt Valley Hospital laboratory. The transcutaneous monitor will be placed on the participant's earlobe (or backup sites as listed above) to measure transcutaneous  $\text{PaCO}_2$  ( $P_t\text{CO}_2$ ), oxygen saturation ( $\text{StO}_2$ ) and heart rate. Finger pulse oximetry will measure oxygen saturation ( $\text{SpO}_2$ ).

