### C. PRIMARY OUTCOME VARIABLE

- i.  $P_t\text{CO}_2$  at completion of the second nebulisation (at  $t=35\text{min}^*$ ), adjusted for baseline.

\*or the last recorded measurement should the  $t=35$  measurement not be obtained (e.g. study terminated early due to rise in  $P_t\text{CO}_2 \geq 10\text{mmHg}$ ).

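### Participants stopped for a PtCO2 rise have their only post-baseline capillary gas after oxygen is removed, and no rule says how that sample enters the PcapCO2 and pH outcomes (secondary i, ii and viii)

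*Protocol*

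**What the plan says.** Protocol Section 6.E.iv(d) sets the usual condition for the second CBG: "The CBG will be taken whilst the air/oxygen-driven nebuliser is still in place". If sampling is technically difficult, the mask comes off no later than t=37.

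The NOTE in the same section deals with participants stopped for a PtCO2 rise of at least 10 mmHg: "from baseline whereby a nebuliser has to be terminated early, the CBG measurement will be taken at this time-point". It then fixes the order: "The top priority if this occurs is removal of oxygen and clinical assessment of the patient. CBG MUST OCCUR AFTER THIS". No maximum interval is stated. Section 6.E.v gives the trigger, where the blinded investigator is to "indicate this to the un-blinded investigator so they can terminate the regimen intervention".

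Section 7.B makes the CBG the source of PcapCO2 and pH ("Capillary blood gas samples (CBG) will measure" both). Section 7.D defines outcomes i and ii "at completion of the second nebulisation (immediately prior to" t=35), and outcome viii as "The proportion of patients with a reduction in pH of" 0.06 or more. It has no provision for early stops. Section 7.C does have one for the primary PtCO2 outcome: "or the last recorded measurement should the" t=35 value be missing. Section 10 specifies analysis by intention to treat.

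**The concern.** One outcome label covers two different measurements. Nearly everyone is sampled on the driving gas. Stopped participants are sampled after the gas has been withdrawn and after a clinical assessment of unstated length. They are selected because their CO2 rose most, and under the trial's own hypotheses they would be mainly in the oxygen arm. Any fall in pCO2 or recovery of pH before sampling would then shrink the difference between arms.

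No other post-baseline CBG is scheduled, so the late sample is the only value these participants have for outcomes i, ii and viii. Setting it to missing would not remove the problem, because that drops the largest responders. At stake are the size of the PcapCO2 and pH differences and the proportion with a pH fall of at least 0.06.

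**Working it through.** **Sample size (not in dispute).** Section 10 gives 82 evaluable patients for a 4 mmHg difference, SD 5.5, alpha 5% (two-sided assumed) and 90% power. A two-sample t calculation gives 41 per arm, 82 in total, with power 0.902. Allocation is 1:1, so 90 recruited gives 45 per arm.

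**The protocol's link between 8 mmHg and 0.06.** Section 8.C ties a pH change of 0.06 to a rise of 8 mmHg. At constant bicarbonate the pH fall is log10((b + rise)/b), where b is baseline pCO2. For a rise of 8 mmHg this gives 0.064 at b = 50 and 0.059 at b = 55, which agrees with the protocol.

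**How close the trigger is to the threshold.** Take a rise of exactly 10 mmHg and assume PcapCO2 has risen as much as PtCO2. A baseline PtCO2 above 60 is excluded. The rise that gives a fall of 0.06 is b × (10^0.06 − 1).

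| Baseline b (mmHg) | pH fall at +10 | Rise giving 0.06 | Drop from +10 that reaches the threshold |
|---|---|---|---|
| 40 | 0.097 | 5.9 | 4.1 |
| 50 | 0.079 | 7.4 | 2.6 |
| 60 | 0.067 | 8.9 | 1.1 |

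On the protocol's own scaling, +10 mmHg corresponds to 0.06 × 10/8 = 0.075, and a drop of 2 mmHg reaches the threshold. Any further drop makes the participant a non-responder.

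**How long such a drop could take.** The document gives no washout rate. With an assumed exponential half-life h, the time from +10 to +8 mmHg is h × log2(10/8). For h = 2, 3, 5, 10 and 15 minutes this is 0.6, 1.0, 1.6, 3.2 and 4.8 minutes. Removing oxygen and assessing the patient could plausibly take that long.

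**Effect on a proportion.** Each misclassified participant costs 1/45 = 2.2 percentage points of that arm. Five in one arm, all misclassified, cost 5/45 = 11.1 points. The five is borrowed from the Section 9 trigger for an earlier safety meeting and is not a forecast.

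**Effect on the mean difference.** The attenuation is (number stopped × mmHg lost before sampling)/45. For one stop losing 2, 5 or 10 mmHg it is 0.04, 0.11 or 0.22 mmHg. For five stops in one arm it is 0.22, 0.56 or 1.11 mmHg. A loss of 10 mmHg means full return to baseline.

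**Which outcomes are exposed.**
- Outcomes i, ii and viii: exposed, because they rest on the CBG alone.
- Outcome vi: worded as PcapCO2 or PtCO2. A PtCO2 rise of 10 already exceeds 4 and 8, so only a separate PcapCO2 tabulation is exposed.
- Outcome vii: counts every stop, so not exposed.
- Primary outcome: uses PtCO2 under its own fallback rule and does not depend on the CBG.

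**The case against.** The protocol never says that early-stop samples are pooled with the others. How off-treatment samples are analysed is ordinary material for a statistical analysis plan, which is not shown. It also says the early-stop CBG is taken when the nebuliser is terminated, so prompt sampling is intended. Time and PtCO2 are recorded as blood enters the capillary tube, so a fall in PtCO2 by then can be seen. Some completers may also be sampled at the moment of mask removal or just after it, given the t=37 limit.

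Most of this is fair. Use of the late sample is an inference, from the absence of any other post-baseline CBG and the intention-to-treat analysis. But the difficulty does not come from a missing analysis detail. The protocol itself fixes a collection rule and an outcome timing that do not match, and it gives an early-stop rule for the primary outcome only. The recorded sampling time is half of what is needed, because no item explicitly asks for the time of stopping.

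Three stronger readings may occur to a reader, and the document does not support them:
- *That the largest responders are lost from every responder outcome, or that hypothesis iii fails.* Outcome vi and hypothesis iii each have a pCO2 limb, stopped participants meet the PtCO2 part of vi through the trigger, and vii counts them.
- *That stopped participants meet a PcapCO2 or pH threshold by definition.* The trigger establishes a PtCO2 rise only, and Section 7.D itself plans to report drift adjustments for PtCO2.
- *That 11 points is the expected loss.* The figure of five is trial-wide, and the calculation needs all five in one arm and all misclassified.

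**Conclusion.** The point stands for secondary outcomes i, ii and viii, and for vi only if PcapCO2 is reported on its own. As written, participants selected for a large response are sampled under a different condition from the rest, after an unlimited delay, and no rule says how the result is used. The bias is toward no difference if stops fall mainly in the oxygen arm, which the hypotheses expect but the document cannot establish.

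The size is 2.2 percentage points per misclassified participant in an arm of 45. The total is unknown, because the number of stops, the delay and the washout rate are not given. The threshold figures assume constant bicarbonate and a PcapCO2 rise equal to the PtCO2 rise. The trial was not powered on these outcomes, so this is a matter of interpreting secondary results and does not threaten the main conclusion. It should still be corrected, because the correction is cheap and the delay may not be recoverable afterwards.

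**What to change.** Leave the care sequence unchanged. In the protocol or the analysis plan:

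1. Reconcile the three timing statements: CBG at the moment of early termination, CBG after oxygen removal and assessment (both Section 6.E.iv), and CBG just before t=35 (Section 7.D, i and ii). State which value represents a stopped participant in i, ii, vi and viii.
2. State that stopped participants meet outcome vi through PtCO2. This is worth writing down because the trigger is read from continuous monitoring and need not coincide with a scheduled reading.
3. Record the time of stopping, so that the delay to the CBG can be reported beside the time and PtCO2 already taken at sampling.
4. Flag these CBGs as off-treatment.
5. Report viii, and any PcapCO2-only proportion, as measured and, as a sensitivity analysis, with stopped participants counted as responders. Add a matching sensitivity analysis for the PcapCO2 and pH ANCOVAs.

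The cost is a few sentences, one case report form field and one extra table. The sample size does not change.

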**v. Regimen monitoring and measurements by the blinded investigator**

- a. At t= 5, 6, 10, 15, 20, 25, 26, 30, 35 record the time, PtCO2 and heart rate.
- b. Continuously monitor PtCO2, and should it increase by  $\geq 10$ mmHg from baseline measure (t=0), indicate this to the un-blinded investigator so they can terminate the regimen intervention.
- c. Record the time and PtCO2 during arterialised earlobe blood gas sampling, as prompted by the un-blinded investigator.

NOTE: The t=20 measure is to occur immediately prior to initiation of the 2nd nebuliser and the t= 15 and t=35 measures are to occur immediately prior to cessation of nebuliser delivery

**F. POST REGIMEN MONITORING**

**i. Intervention**

The un-blinded investigator is to document the nasal prong oxygen flow instituted at the end of the second nebuliser.\* Until t=80 oxygen will be delivered at this flow rate via nasal cannulae, except if the SpO2 falls to <85%. In this case the flow is to be titrated until the 88-92% target saturation range is met.

\* If participant has been on the air driven regimen, this will be the titrated flow at t=35. If participant has been on the oxygen driven nebuliser this will be the flow delivered via nasal prongs prior to the last nebulisation (t=20 min).

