### **C. HYPOTHESES**

- i. Oxygen driven bronchodilator nebulisation results in increased pCO2 in exacerbations of COPD compared with air driven bronchodilator nebulisation
- ii. Oxygen driven bronchodilator nebulisation results in a reduction in pH in exacerbations of COPD compared with air-driven bronchodilator nebulisation
- iii. The increase in pCO2 and reduction in pH secondary to oxygen-driven nebuliser use are clinically significant in some patients, defined as  $\geq 8$ mmHg change in PaCO2 or  $\geq 0.06$  change in pH.
- iv. Clinically significant elevations in pCO2 secondary to oxygen-driven nebuliser use occurs within six minutes of commencement of nebulisation in some patients
- v. Cessation of oxygen-driven bronchodilator nebulisation may result in rebound hypoxaemia

---

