## **iii. Regimens**

### Air driven nebuliser regimen

- a. t=0-15 min: 2.5 mg salbutamol by nebulisation, delivered by air at a flow rate of 8L/min
- b. t=15-20 min: Removal of nebuliser mask
- c. t=20-35 min: 2.5 mg salbutamol by nebulisation, delivered by air at a flow rate of 8L/min.

The nebuliser is to continue running for the entire 15 minutes at t=0-15 min and t=20-35 min, even if the bronchodilator medication has dissipated.

Oxygen therapy is to be continued to be titrated by the un-blinded investigator using nasal cannulae (worn under the nebuliser mask at 0-15 and 20-35 min). Note that if the patient was not receiving oxygen before the intervention (was breathing room air) this will continue unless the oxygen saturations drop to <85%. If this occurs the nebuliser mask will be removed, nasal prongs attached and oxygen given before reattaching the nebuliser mask. If this does happen it will be recorded in the case report form.

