## 8. Methodology notes

### A. WASH IN, REGIMEN AND OBSERVATION PERIODS

Delivery of two 15 minute nebulisers with a 5 minute gap with a 2.5mg salbutamol dose were selected to represent real-life nebuliser delivery in the acute setting. Titration of oxygen before and during the regimens represents recommended evidence based on best practice.

Maintenance of any nasal cannulae oxygen therapy at a constant flow during the observation period is designed to assess the risk of rebound hypoxia (a reduction in SpO2 following abrupt cessation of oxygen therapy to below the baseline level prior to instituting oxygen therapy). To detect any rebound hypoxemia a constant fraction of inspired oxygen is required. The results would represent the risk of rebound hypoxia in the situation that oxygen saturation monitoring does not occur following the abrupt cessation of high concentration oxygen therapy.

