## **10. Power and Statistical Methods**

A difference in  $PaCO_2$  of 4 mmHg represents a physiologically significant change.  
 In our controlled study of oxygen versus air driven nebulisers in stable COPD the standard deviation of  $P_tCO_2$  was 5.5. With 90% power and alpha of 5% this requires a total of 82 patients to detect a 4 mmHg difference. We anticipate a drop-out rate of <10% so our target recruitment is 90 patients. Analysis will be by intention to treat. Participants recruited will be stratified in to groups that were receiving oxygen immediately prior to randomisation or those that were not. Our primary analysis is ANCOVA with  $P_tCO_2$  as the response variable, and randomised treatment and baseline  $P_tCO_2$  as co-variables. For other continuous outcome variables we will also use similar ANCOVA. Exploratory analyses for  $P_tCO_2$ , heart rate and  $SpO_2$  taken at five minute intervals will be presented graphically and analysed by mixed linear models.

---

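### Rebound hypoxaemia (hypothesis v) has no outcome of its own, and the two outcomes that bear on it, serial SpO2 and oxygen-flow increases, measure it poorly

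*Protocol*

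**What the plan says.** Hypothesis v in protocol section 2.C reads: "Cessation of oxygen-driven bronchodilator nebulisation may result in rebound hypoxaemia". Section 8.A defines rebound as a drop in SpO2 "following abrupt cessation of oxygen therapy to below the baseline level prior to instituting oxygen therapy", and sets a condition for seeing it: "To detect any rebound hypoxemia a constant fraction of inspired oxygen is required".

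Section 6.F.i fixes the nasal flow from the end of the second nebuliser to t=80, with an exception when SpO2 drops below 85%: "In this case the flow is to be titrated until the 88-92% target saturation range is met". Its footnote sets the fixed flow by arm. For air: "If participant has been on the air driven regimen, this will be the titrated flow at t=35". For oxygen it is the t=20 flow, which under section 6.E.iii is normally the t=0 flow.

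Two secondary outcomes in section 7.D are relevant. Outcome iv takes PtCO2, SpO2 "and heart rate at 5 minute intervals from" t=0 to t=80. Section 10 says such data "taken at five minute intervals will be presented graphically and analysed by mixed linear models" and labels this exploratory. Outcome ix is the proportion of patients needing more oxygen flow, over the regimen and observation periods together.

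Section 6.F.ii has SpO2 recorded at nine scheduled points (t=40 to t=80) and, at any flow change, the time and the new flow.

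**The concern.** A stated hypothesis should have an outcome that answers it. PtCO2 has a greatest-change-from-baseline outcome (7.D v); SpO2 has no counterpart, although hypothesis v is about a fall in SpO2.

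The SpO2 series is a weak substitute. Anyone who drops below 85% after the nebuliser stops has flow raised until saturation recovers, and the recovered readings belong to the same series. These are the participants with the clearest rebound, so the bias is towards finding none. Outcome ix would catch them, but it mixes them with increases made for other reasons in an earlier period. The trial could report a small mean SpO2 difference and an uninformative difference in oxygen increases when a real rebound had occurred in a minority of the oxygen arm.

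**Working it through.** **The plan's own figure.** The protocol gives no figure for SpO2 or rebound. Its only sample-size figure is for PtCO2 (difference 4 mmHg, SD 5.5, two-sided 5%, 90% power). A two-sample t calculation gives 40.7, so 41 per arm and 82 in total, as stated. It is not affected by this point.

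**Step 1: the constancy condition against the flow rule.** Section 8.A requires a constant inspired fraction. Section 6.F.i keeps flow constant only while SpO2 stays at or above 85%. The two agree for shallow falls and conflict for the deepest. Outcome iv runs to t=80 and nothing in sections 7.D or 10 separates readings before and after an increase.

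**Step 2: what outcome ix counts, by period.**

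| Period | Air arm | Oxygen arm |
|---|---|---|
| t=0-35 | Nasal oxygen titrated throughout (6.E.iii): "Oxygen therapy is to be continued to be titrated by the un-blinded investigator using nasal cannulae" | Cannulae off while the nebuliser runs; restarted at a fixed flow |
| t=35-80 | Fixed flow; increase only if SpO2 <85% | Fixed flow; increase only if SpO2 <85% |

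In the second row an increase is, by rule, a hypoxaemia event in either arm. In the first row an air-arm participant on nasal oxygen can have an ordinary titration increase, with no equivalent in the oxygen arm during nebulisation. Section 6.E.iv also asks for flow changes to be documented in the air arm only. Pooling the rows can offset an excess of later events in the oxygen arm.

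**Step 3: the flow at which the arms are compared.** The oxygen arm normally returns to its t=0 flow; the air arm stays on its t=35 flow, which may differ from t=0. The between-arm SpO2 contrast may therefore not be at baseline flow. Section 8.A's definition is within person, so this does not affect detection within the oxygen arm.

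**Step 4: illustrative size (all inputs assumed).** The simplest form is bias in the arm mean = proportion rescued × points restored: 0.15 × 5 = 0.75 points, with a range of 0.10 × 5 = 0.5 to 0.20 × 6 = 1.2. This supposes that the dip would otherwise have lasted in full.

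A simulation lets the dip fade:

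- Baseline SpO2 ~ N(90, 1.2²); dip = max(0, N(m, 2²)).
- SpO2(t) = baseline − dip × s(t), where s(t) = (t−35)/6 up to t=41, then exp(−(t−41)/τ).
- From 2 minutes after the first minute below 85%, SpO2 is at least 90.
- Change is averaged over the nine scheduled readings.

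| m (points) | τ (min) | Rescued | Mean change, no rescue | Mean change, recorded | Attenuation | Rescued with a scheduled reading <85% |
|---|---|---|---|---|---|---|
| 2 | 10 | 9.9% | −0.60 | −0.41 | 0.19/0.60 = 32% | 4.7/9.9 = 47% |
| 2 | 20 | 9.8% | −0.97 | −0.70 | 0.27/0.97 = 28% | 4.7/9.8 = 48% |
| 5 | 10 | 49.9% | −1.39 | −0.50 | 0.89/1.39 = 64% | 28.8/49.9 = 58% |
| 5 | 20 | 50.1% | −2.24 | −0.84 | 1.40/2.24 = 63% | 28.7/50.1 = 57% |

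Under these assumptions the mean fall is cut by about 28% to 64% but keeps its sign. The value that triggered the increase often falls between scheduled readings, where section 6.F.ii does not ask for it to be recorded.

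**The case against.** A reader might infer that rebound is tested only through SpO2 readings. It is not: outcome ix counts flow increases, and section 6.F.ii time-stamps each one in the observation period, so rescued participants can be identified. That stands. What remains is that outcome ix as defined pools two unlike periods.

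A reader might also infer that a true rebound could be erased. The documents do not support this. Falls that stay at or above 85% trigger no increase and remain fully visible; deeper falls are blunted in the series and still counted in outcome ix.

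The air arm's t=35 flow might be thought to spoil the test altogether. It bears only on the between-arm contrast, because rebound is defined against a person's own baseline and the arm in question normally returns to its baseline flow.

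Two further objections are fair. How the mixed model treats readings after an increase is commonly settled in the analysis plan, which is not at hand, so silence on it is not itself a fault. The outcome list and the data to be recorded, however, are fixed in the protocol. And the analysis is labelled exploratory for a hypothesis worded as a possibility, which limits the weight of the point without removing the mismatch.

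**Conclusion.** The point holds in limited form. Hypothesis v has no matching outcome. The SpO2 series, followed as written, departs from section 8.A's own condition in those with the deepest falls and leans towards no rebound. Outcome ix mixes observation-period events with regimen-period increases that can arise differently in the two arms.

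The direction follows from the protocol's rules; the size does not. The protocol gives no SpO2 standard deviation, rescue rate or expected dip, so the 28% to 64% attenuation and the 0.5 to 1.2 points only illustrate stated assumptions. The PtCO2 primary analysis and the sample size are untouched. This is worth correcting because almost all the data needed are already collected.

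**What to change.** - Add a secondary rebound outcome: the lowest SpO2 after the second nebuliser stops, to t=80, using readings up to and including the one that triggers the first flow increase. The t=35 reading is excluded because it is taken with the nebuliser still running. Compare arms by ANCOVA with t=0 SpO2 as covariate. The between-arm comparison is essential, since the minimum of several readings lies below a single baseline reading by noise alone.
- Report outcome ix (SpO2 <85% or a flow increase) separately for t=35-80.
- Record the triggering SpO2 at any flow change.
- Add a sensitivity version of the SpO2 mixed model that omits readings after a flow increase.
- State that the air arm is observed at its t=35 flow, so the between-arm SpO2 contrast may not be at baseline flow.

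Restricting an analysis to participants whose post-regimen flow equals their t=0 flow is not advised. It conditions on a post-randomisation variable, which nearly all the oxygen arm would meet by rule while the air arm would be selected by its titration history.

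These are changes to measurement and analysis only; the rescue rule is left as it is. The cost is one case report form field, some protocol wording, and fewer readings in the sensitivity analysis.
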